
#### Environmental Data

The retrospective weather and environmental data are collected from freely accessible datasets provided by the German Meteorological Service (DWD) and the Federal Environment Agency (UBA). The DWD provides data sets comprising hourly and daily aggregated data on air temperature, humidity, wind speed, and precipitation. The Federal Environment Agency provides datasets on air quality at an hourly level on ozone (O₃), nitrogen dioxide (NO₂), particulate matter (PM10 [particulate matter with a diameter ≤10 µm] and PM2.5 [particulate matter with a diameter ≤2.5 µm]), and sulfur dioxide (SO_2_). For the regular use case Stuttgart, data on global radiation, radiation balance, as well as UV-A and UV-B radiation will also be available. The weather and environmental data of Stuttgart will be sourced from an environmental monitoring station located in the valley basin, approximately 1.3 km from the clinic. In addition, pollen count data will be acquired from the German Pollen Information Service foundation (*Polleninformationsdienst* [PID]). The PID operates various pollen measuring stations in Germany, where the pollen concentration of various allergenic plants and trees is measured and counted on a daily basis. The pollen types with the highest allergic potential for humans will be selected together with experts from the PID.

#### Area-Level Socioeconomic Deprivation

Area-level socioeconomic deprivation will be operationalized using the German Index of Socioeconomic Deprivation (GISD), a composite measure developed by the Robert Koch Institute that summarizes relative regional deprivation across education, employment, and income dimensions and is available at multiple spatial levels (eg, municipality and district) for different years. Patients’ residential postal codes will be mapped to GISD values and used to assess socioeconomic gradients and potential effect modification of heat–outcome associations.

### Outcomes

We defined one primary objective with a corresponding primary outcome (O1), a set of secondary clinical and usage objectives and outcomes (O2-O5), and exploratory methodological objectives and outcomes related to a prospective substudy, syndromic surveillance, and prediction modeling (O6-O8). All exposure definitions and analytical decisions are specified in the statistical analysis plan.

### Primary Outcome: Daily All-Cause ED Usage (O1)

We will quantify the number of ED encounters per participating hospital and calendar day (hospital-day level; AKTIN encounter identifier aggregated by clinic × date).

### Secondary Outcomes (O2-O5)

#### Daily Admission Rate From the ED (O2)

We will use the proportion of ED encounters resulting in inpatient admission per hospital and day (hospital-day level; derived from encounter disposition and admission fields using AKTIN encounter identifier aggregated by clinic×date).

#### Syndromic and Diagnostic Case-mix (O3)

We will quantify daily counts and proportions of prespecified diagnostic and syndromic categories, including heat-sensitive conditions and shifts in major diagnosis group distributions (hospital-day level; derived from ED *ICD-10-GM*, inpatient discharge *ICD-10-GM*, and CEDIS-PCL).

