### Primary Objective (Prespecified Retrospective Analysis)

Objective 1 (O1): the primary objective is to quantify the association between ambient heat and acute-care demand in Germany, using a prespecified retrospective analysis of daily ED visit volumes as primary outcomes. We will compare heat days with comfort days, quantify exposure–response relationships, and characterize immediate and delayed effects of heat over predefined lag windows as the primary objective. In addition, we will identify temperature thresholds at which ED attendances and hospital admission probabilities increase and assess whether these associations differ across vulnerable patient groups, with a focus on children, older, and people with multiple comorbidities.

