### Secondary Clinical Objectives (Retrospective; Secondary Endpoints)

Objective 2 (O2): we will analyze hospital admission rates related to heat exposure.

Objective 3 (O3): we will examine shifts in syndromic and diagnostic patterns on heat days.

Objective 4 (O4): we will assess pathways to emergency care, including referral source and mode of transport, by applying suitable models for compositional or proportion outcomes.

Objective 5 (O5): we will assess clinical severity at ED presentation using routinely recorded proxies, including triage acuity and high-acuity presentation rate.

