#### Routine ED Records

Retrospective data will be sourced from the AKTIN Registry [27]. The registry is implemented on the underlying AKTIN infrastructure, a nationwide federated data network operated within the Network University Medicine [28]. For the study, a total of 56 EDs throughout Germany, including clinics of different care levels in cities with different population sizes, provide electronic health records from all ED visits documented in the respective ED in the years 2019 to 2024.

Across participating EDs, approximately 6.35 million ED visits will be available for the study period, with an anticipated exclusion of up to 10% due to missing key variables. This retrospective ED dataset contains patient-specific information on age, sex (male, female, or other), and the zip code of the patient’s place of residence, as well as administrative data on mode of transport to the ED, time of admission, and mode of disposition (discharge to home, transfer to other hospital, inpatient admission, or death). Furthermore, it contains the following treatment information: ED diagnoses in the form of *ICD-10-GM* (*International Classification of Diseases and Related Health Problems, Tenth Revision, German Modification*) codes with a labeling of the main ED diagnosis, additional information on diagnosis certainty (secured, suspicion of, condition after or exclusion of diagnose), chief complaint in the form of Canadian Emergency Department Information System – Presenting Chief Complaints (CEDIS-PCL) codes, urgency level coded as Manchester Triage System (MTS) or Emergency Severity Index (ESI), vital parameters, Glasgow Coma Scale (GCS) and isolation status [29-31]. In case of an inpatient admission following the ED visit, inpatient treatment information according to the German social laws regulating the billing of inpatient services (§ 21 Krankenhausentgeltgesetz, KHentG) is available. This information contains the inpatient discharge diagnosis, also coded as *ICD-10-GM*. Multiple ED visits by the same person during the study period cannot be attributed due to data protection requirements.

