##### Prediction Model Performance (O8)

We will quantify accuracy of weather-informed models forecasting daily ED usage and related usage metrics (hospital-day forecast level; evaluated across hospitals, dates, and times).

Across objectives O1-O5, we will evaluate whether associations differ across vulnerable patient groups (eg, age, sex, and multimorbidity proxies) and by area-level vulnerability indicators, including socioeconomic deprivation (GISD) and urban–rural context. All exposure definitions and analytical decisions are specified in the statistical analysis plan.

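### O3 case-mix categories draw partly on discharge codes that exist only for admitted patients, so part of an apparent heat-day shift can follow the admission share rather than incidence

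*Protocol article*

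**What the plan says.** Under Syndromic and Diagnostic Case-mix (O3), the protocol article states: "We will quantify daily counts and proportions of prespecified diagnostic and syndromic categories, including heat-sensitive conditions". The level is the hospital-day and the categories are "derived from ED *ICD-10-GM*, inpatient discharge *ICD-10-GM*, and CEDIS-PCL". The aim, under Secondary Clinical Objectives, is stated as "we will examine shifts in syndromic and diagnostic patterns on heat days".

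The section Routine ED Records says who has the third source: "In case of an inpatient admission following the ED visit, inpatient treatment information according to the German social laws" is available. It adds: "This information contains the inpatient discharge diagnosis, also coded as *ICD-10-GM". An encounter that ends in discharge home, transfer to another hospital or death in the ED therefore has no such code.

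Admission is a study outcome in its own right. O2 is "the proportion of ED encounters resulting in inpatient admission per hospital and day", and the primary objective also sets out to "identify temperature thresholds at which ED attendances and hospital admission probabilities increase".

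The article gives no rule for combining the three code sources, sets no admitted-only denominator for discharge codes, and plans no version of O3 based on ED codes alone. The paragraph that closes the outcomes section refers analytical decisions to the statistical analysis plan, which is not available here. The same paragraph lists effect modification by "vulnerable patient groups (eg, age, sex, and multimorbidity proxies") without saying how the proxies are built.

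**The concern.** O3 is meant to show whether the mix of conditions presenting to the ED changes on hot days. One of its sources is present or absent according to a decision taken after presentation, and the study expects that decision to vary with heat. If more patients with a given condition are admitted on heat days, more of them acquire a discharge code and more are counted, although no more of them came. If fewer are admitted, the count falls. Either movement would be read as a shift in morbidity.

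The clinical message of O3 is what is at stake. The Discussion expects heat-related patterns for dehydration and heat illness, renal disease and cardiopulmonary disease. It also argues that ED data show such effects earlier than discharge diagnoses do. An O3 category that depends partly on discharge codes weakens that argument and makes O3 and O2 hard to interpret as separate findings.

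**Working it through.** The documents give no O3 prevalence, admission rate, code-capture rate or effect size, so there is no figure of the plan to reproduce. What can be checked is how a category count responds to admission alone.

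**Inputs (all assumed, none from the documents)**
- sE: probability that a true case is captured by a source available for every encounter (ED ICD-10-GM or CEDIS-PCL), 0.3 to 0.5.
- sI: probability that an admitted true case is captured by a discharge code, 0.6 to 0.8, independent of sE.
- a: admission share among patients with the condition, 0.40 on comfort days and 0.42 or 0.45 on heat days.
- True incidence and total encounters: unchanged.
- Combination rule: a case counts if any source is positive.

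**Formula**

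Captured fraction D(a) = a × [1 − (1 − sE)(1 − sI)] + (1 − a) × sE = sE + a × (1 − sE) × sI.

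Apparent heat/comfort ratio = D(heat) / D(comfort). With no true change this should be 1.

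**Results at all four corners of the assumed grid**

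| sE | sI | D(0.40) | D(0.42) | D(0.45) | Ratio, 42% | Ratio, 45% |
|---|---|---|---|---|---|---|
| 0.3 | 0.8 | 0.524 | 0.5352 | 0.552 | 1.021 | 1.053 |
| 0.3 | 0.6 | 0.468 | 0.4764 | 0.489 | 1.018 | 1.045 |
| 0.5 | 0.8 | 0.660 | 0.668 | 0.680 | 1.012 | 1.030 |
| 0.5 | 0.6 | 0.620 | 0.626 | 0.635 | 1.010 | 1.024 |

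The apparent increase is 1.0-2.1% when admission rises to 42% and 2.4-5.3% when it rises to 45%.

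**Outside that grid** (sI = 0.8, admission up 10% in relative terms, 0.40 to 0.44)
- sE = 0 (category rests on discharge codes alone): ratio 0.44/0.40 = 1.100, fully proportional to the admission change.
- sE = 0.7: (0.7 + 0.44 × 0.24)/(0.7 + 0.40 × 0.24) = 0.8056/0.796 = 1.012.
- sE = 0.9: (0.9 + 0.44 × 0.08)/(0.9 + 0.40 × 0.08) = 0.9352/0.932 = 1.003.
- sE = 1: ratio 1.000.

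**Direction.** A 10% relative fall (0.40 to 0.36) gives 0.957 at sE = 0.3 and 0.976 at sE = 0.5. Under this counting rule the artefact takes the sign of the admission change, and the documents do not say which sign that is.

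**After the fix.** If only sources available for every encounter are used, D = sE whatever the value of a, and the ratio is exactly 1.000.

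**The case against.** The strongest reply is that the article only lists three sources. It does not say that an encounter counts when any one of them is positive, or that discharge codes share an all-encounter denominator. Three separate series would fit the same sentence, and the unseen analysis plan may say so. It is true that pooling is the natural reading but not an explicit one, which is why the point is stated conditionally. The reply does not dispose of the matter, because the article itself fixes the sources and the hospital-day level of the outcome. If the analysis plan keeps discharge codes apart, the mechanical link disappears, though selection into admission remains.

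A second reply is that chief complaints add capture that does not depend on admission, and that O2 is reported anyway, so a change in admission would be visible. Both are fair. The first shrinks the artefact, as the working shows. The second helps a careful reader but does not separate the two effects.

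Four stronger readings are tempting and are not supported:
- A reader might infer that O3 shifts as a whole track the admission share. That holds only for categories resting on discharge codes alone. Elsewhere the effect is diluted.
- A reader might infer that multimorbidity in this study partly means being admitted. Repeat visits cannot be linked, so codes from the index encounter are a likely source, but the article does not define the proxies or tie them to discharge codes.
- A reader might infer that the artefact is as large as the heat effects being sought. The article gives no expected effect for its own study. The one all-cause figure it cites is a 17% increase in US children's hospitals, which is well above 1-5%.
- A reader might assume that discharge codes are more complete than ED codes or include conditions acquired in hospital. The documents do not say so, and the argument needs only that discharge codes add or change some classifications.

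**Conclusion.** The point holds in conditional form. One of the three O3 sources exists only after admission, admission is itself a heat outcome, and nothing in the article keeps the two apart. Where a discharge code can add or change a category among all encounters, part of a heat-day shift can arise with no change in incidence.

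The true size and direction are unknown. The illustrative 1.0-2.1% and 2.4-5.3% rest on the assumed capture rates, the assumed 40% admission among cases, independence of the sources and an any-source counting rule. The effect could be negligible for well-coded conditions and fully proportional to the admission change for categories seen only at discharge.

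This is a moderate issue confined to a secondary outcome. O1 counts encounters without using diagnosis codes and is not affected.

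**What to change.** Define the main O3 categories only from sources available for every encounter, ED ICD-10-GM and CEDIS-PCL. Report discharge-diagnosis categories as a separate analysis with an admitted-only denominator, label it case mix of admissions, and present it alongside O2. As a precaution, state that discharge codes are not used in any multimorbidity proxy that serves as an effect modifier of admission.

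The cost is a short change of wording and one separate analysis. The downside is lower sensitivity for some categories in the main O3 analysis, and the separate discharge-code analysis retains that information for admitted patients. The Results section schedules the health care research analysis to be finalised by April 1, 2026, so the rule should be fixed before O3 results are produced. If they already exist, the restricted version should be reported and the change dated.

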#### Access Pathways (O4)

We will analyze the daily distribution of referral sources and mode of transport to the ED (hospital-day level; derived from encounter-level pathway variables such as transport and referral).

#### Severity Proxies (O5)

We will use daily distribution of acuity and clinical severity indicators at presentation (hospital-day level; derived from triage categories, high-acuity proportions, and additional severity proxies such as vital signs or Glasgow Coma Scale).

#### Ancillary Prospective Geriatric Substudy: Heat-Related Symptom Burden in Older Adults (O6)

We will characterize patient-reported heat-related symptoms and functional impact using structured questionnaires at prespecified assessment time points (participant-level, derived from questionnaires on quality of life, mobility, social background, and heat-related behavior).

#### Exploratory Outcomes (O7-O8)

##### Syndromic Surveillance (O7)

We will create syndrome definitions to identify cases of climate change-related ED visits in the routine data and validate their performance by comparing them with different reference data sources (heat-related syndromic indicators).

##### Prediction Model Performance (O8)

We will quantify accuracy of weather-informed models forecasting daily ED usage and related usage metrics (hospital-day forecast level; evaluated across hospitals, dates, and times).

Across objectives O1-O5, we will evaluate whether associations differ across vulnerable patient groups (eg, age, sex, and multimorbidity proxies) and by area-level vulnerability indicators, including socioeconomic deprivation (GISD) and urban–rural context. All exposure definitions and analytical decisions are specified in the statistical analysis plan.

### Data Linkage

The linkage between patient data and environmental data is established at the hospital level. For each hospital, the nearest weather station with the smallest air distance is identified, ensuring that there are fewer than 500 missing values within the time interval of 2019-2024. Due to the limited spatial availability and completeness of air quality data, air data are matched solely based on proximity to the hospital, accepting some missing values. Both the weather and air quality data are provided as hourly records, as well as in a summarized format with daily minimum, maximum, and mean values. The spatial granularity is selected to be as fine as possible. However, a finer granularity is not feasible due to data policy restrictions on patient data and the limitations of the environmental measurement grid. Under the assumption that environmental phenomena generally occur on a large scale and that most patients choose the nearest ED in case of an emergency, the linked data provide at least an approximate overview of the environmental influences to which patients were exposed before the onset of their illness. Following scientific best practices and ensuring reproducibility, the Python code used for the data linkage is publicly available on GitHub [35]. The pollen stations will be selected in consultation with experts from the PID, considering data completeness as well as proximity to the ED (Figure 1).

**Figure 1 figure1:**
[figure not shown]
Overview of data sources, linkage, and analysis. DWD: German Meteorological Service (Deutscher Wetterdienst); ED: emergency department; GSID: German index of socioeconomic deprivation; PID: Polleninformationsdienst; UBA: Federal Environment Agency (Umweltbundesamt).

### Data Protection

A scientific advisory board has been established, comprising representatives from medical associations (including the German Interdisciplinary Association for Intensive Care and Emergency Medicine and the German Society for Interdisciplinary Emergency and Acute Medicine), clinical experts specializing in emergency medicine, and a patient representative from the German Coalition for Patient Safety (*Aktionsbündnis Patientensicherheit* e.V., Berlin). Additional experts from the Federal Office for Citizen Protection and Disaster Support (*Bundesamt für Bevölkerungsschutz und Katastrophenhilfe*) and the DWD are involved. The purpose of this board is to offer scientific guidance for the project, advocate for the interests of patients, and assist in implementing the outcomes.

### Ethical Considerations

#### Ethics Approval

This study was approved by the leading ethics committee at the Medical Faculty of the University of Magdeburg (29/24 dated March 08, 2024), as well as by the institutional ethics committee at RWTH Aachen (24-333 dated October 10, 2024).

#### Informed Consent

The use of the ED data has been approved by the AKTIN Data Use and Access Committee and is subject to AKTIN’s data protection regulations. Written informed consent will be obtained from all patients participating in the ancillary prospective geriatric substudy. Both the retrospective registry-based study and the ancillary prospective geriatric substudy are registered in the DRKS and are governed by their respective approvals (AKTIN data access for retrospective analyses; site-specific ethics and informed consent for the prospective substudy).

#### Privacy and Confidentiality

Data are processed in compliance with applicable data protection regulations. The dataset used for analysis is pseudonymized at source and direct identifiers are not available to the study team. Data transfer and storage are secured (encrypted transfer, access restricted to authorized personnel, analysis on secure servers), and results are reported only in aggregated form.

#### Compensation

Geriatric participants will receive no compensation.

### Statistical Methods

The statistical analysis will be conducted using R (R Development Core Team).

#### Descriptive Overall Population Analyses

The descriptive analysis of the overall population will characterize the overall cohort and support the planning of relevant subgroup analyses. It will include key aspects of the cohort based on multiple variables, including sociodemographic factors (age and gender), presenting complaints (CEDIS-PCL), initial triage assessment (MTS or ESI), patient referral pathways, hospital stay duration, discharge outcomes, diagnostic categories (*ICD-10-GM*), and socioeconomic status (GISD). Continuous variables will be summarized using mean (SDs) or median (IQRs), and categorical variables as counts and percentages. Distributions will be presented graphically (eg, histograms and density plots).

#### Statistical Modeling of Environmental Factors on ED Visits (O1-5)

The number of all-cause ED visits in relation to temperature and environmental factors will be investigated using a 2-stage analysis approach. In the first stage, given the available data, we plan to fit the site-specific number of daily ED visits using a quasi-Poisson regression model including a distributed lag nonlinear model for daily temperature to capture delayed temperature effects, using appropriate splines and lags [34].

These models aim to adjust for seasonal trends in temperature and air quality using smooth functions and will additionally include day of week, public holidays, and further covariates (O₃, NO₂, particulate matter [PM10 and PM2.5], SO_2_, UV-A, UV-B radiation, and predefined pollen). Heat days, one of the main focuses of this study, will be defined a priori based on clinic-specific temperature distributions (days with mean air temperature above the 95th percentile), and alternative operationalizations (eg, heat index, tropical nights, and heatwaves) will be examined in prespecified sensitivity analyses. The analysis is planned to be stratified by age group (0-5 years, 6-11 years, 12-17 years, and ≥65 years). In the second stage, ED-specific distributed lag nonlinear model coefficient vectors are planned to be pooled using a random-effects meta-analysis approach to obtain an overall heat exposure–response association and to quantify between-site heterogeneity [34]. As sensitivity analysis, we will assess the robustness of our modeling choices, including alternative lag windows, splines, and alternative number of knots for temperature and lag. We will also investigate the sensitivity when using other alternative stratification strategies and missing data handling. A detailed statistical analysis plan will be prepared in advance of the data analysis.

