**Methods:**

KlimaNot is a multicenter, registry-based observational cohort study with retrospective and prospective components. The primary analysis is a prespecified retrospective evaluation using routinely collected encounter data from the German National Emergency Department Data Registry (AKTIN), comprising approximately 6.35 million ED visits from up to 56 EDs (2019-2024). Hospital-level environmental exposures (eg, temperature and selected air pollutants) will be linked to each participating ED based on location and summarized to daily metrics. The primary endpoint is daily all-cause ED visit volume at the hospital-day level. Secondary endpoints include hospital admission probability, syndromic and diagnostic case-mix, referral source and mode of transport, and routinely recorded proxies of clinical severity (eg, triage acuity). Heat effects will be quantified using models allowing for nonlinear exposure–response relationships and delayed (lagged) effects, with adjustment for site, seasonality and time trends, weekday, and public holidays; effect modification by age, sex, multimorbidity proxies, and area-level socioeconomic deprivation will be assessed. Additional analyses include a predefined case study for the region Stuttgart, leveraging extended longitudinal and more detailed pathway data, development and validation of heat-sensitive syndromic surveillance indicators, evaluation of short-term forecasting models of ED usage, and an ancillary prospective geriatric substudy collecting patient-reported and functional outcomes to better characterize vulnerability in the oldest-old.

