Although there is already extensive evidence on the impact of weather and the environment on population health, the influence of weather-related factors on the use of EDs is still not sufficiently understood**.** While there is unambiguous evidence of a positive association between high ambient temperatures and ED visits due to directly heat-sensitive diseases such as dehydration and electrolyte imbalances, there is inconclusive evidence on the relationship between temperature and cardiovascular, renal, and respiratory diseases [18-20]. EDs serve as a central element of the German health care system and provide crucial insights into current emergency and acute medical care trends. Given the ubiquitous effects of global climate change and the existing evidence, we hypothesize that climate-change-related weather conditions, such as extreme heat days, significantly influence population health and the usage of EDs in Germany. Moreover, we assume geographical differences and a group-specific impact on children, older, and patients with multiple comorbidities.

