## Discussion

### Anticipated Findings

This multicenter, registry-based observational study will provide valuable insights into the impact of climate change-related weather phenomena on emergency and acute care services in Germany. Because ED contacts capture acute decompensations and time-critical presentations at the front door of the health system, routinely collected ED data can provide early signals of weather-sensitive health impacts and short-term burden. These impacts often become evident before they are fully reflected in downstream outcomes such as hospital discharge diagnoses or mortality statistics. Within this sentinel framing, we anticipate that extreme heat will be associated not only with changes in overall ED volume, but also with measurable shifts in the composition of presentations and care pathways. We assume that heat exposure will be associated with measurable increases in overall ED usage and diagnosis-specific patterns consistent with heat sensitivity (eg, dehydration and heat illness, renal diseases, and cardiopulmonary diseases). We further expect that associations will be heterogeneous across patient groups, with stronger relative effects in vulnerable populations such as children and adolescents, and older patients or those with multiple comorbidities, consistent with prior evidence on heat-related morbidity gradients [17,36,37]. Prior research has documented associations between high temperatures and a broad range of acute morbidity outcomes, including ED visits and emergency hospitalizations, with differential impacts by age and comorbidity [15,21,38,39]. However, many large-scale studies still rely on mortality or hospital admission endpoints, and ED-based analyses often focus on visit counts or diagnosis groups, which can limit the characterization of operationally relevant care pathways and disposition and admission patterns as distinct outcomes [21,38]. In particular, multicenter ED studies that jointly assess volume, case mix, and pathway-related endpoints remain limited. ED-based syndromic surveillance can support situational awareness since EDs capture acute presentations in near real time. In Germany, routine data from the AKTIN ED registry provide an important basis for such monitoring [27]. In this project, syndromic surveillance will be operationalized using *ICD-10-GM* and CEDIS-PCL codes, and the proposed heat-related syndrome definition will be developed and empirically tested. Syndromic surveillance of heat-related visits can complement predictive models by providing timely signals for estimating and tracking heat-related illness at the population level [22]. The main goal of this study is to produce results that can be compared across different sites and that are useful for preparedness and prevention. The findings may help EDs plan their staffing and capacity during forecasted heat days and heat periods, supporting public health surveillance and guiding targeted prevention for high-risk groups. By looking not only at ED usage, but also at changes in case mix and pathways of care, the project aims to build a more complete preparedness approach that reflects how acute care works across sectors such as ED, emergency medical service, outpatient care, and inpatient beds. The results are likely to apply best to ED settings that are similar to the participating sites in terms of documentation practices, catchment area, and the quality of linking ED data to environmental exposure data.

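### The listed age strata leave out patients aged 18-64, so the expected stronger heat effect in children and older people has no separate, non-vulnerable reference group

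*Protocol article*

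**What the plan says.** Under Statistical Modeling of Environmental Factors on ED Visits (O1-5), the article describes a two-stage analysis: site-specific quasi-Poisson distributed lag nonlinear models, then random-effects pooling. On age it says "The analysis is planned to be stratified by age group (0-5 years, 6-11 years, 12-17 years, and ≥65 years". The list carries no marker that it is only an example, and no reference group is named. The same section adds a sensitivity analysis with alternative stratifications, which it does not describe.

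Several other places set up a comparison by age:

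- Abstract, Methods: "effect modification by age, sex, multimorbidity proxies, and area-level socioeconomic deprivation will be assessed".
- Primary Objective: the study will "assess whether these associations differ across vulnerable patient groups, with a focus on children, older, and people with multiple comorbidities".
- Background: "we assume geographical differences and a group-specific impact on children, older, and patients with multiple comorbidities".
- The closing paragraph on outcomes, after O8, repeats the plan to look at differences by age across O1-O5.
- Anticipated Findings: associations are expected to vary, "with stronger relative effects in vulnerable populations such as children and adolescents, and older patients or those with multiple comorbidities".

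The data do not force the gap. Routine ED Records says the sites supply "electronic health records from all ED visits documented in the respective ED in the years 2019 to 2024", and patient age is among the variables.

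**The concern.** To say that an effect is stronger in one group is to compare it with another. Here the natural comparator is adults of working age, whom the article nowhere describes as vulnerable because of their age. Its own background reports higher relative risks in people aged 65 and over relative to younger adults. The stated strata leave that group out.

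At stake is how the age-specific results can be read. Without a separate reference, a reader would have to compare one vulnerable group with another, or a vulnerable group with a total that includes it. The first can show no difference although both groups are at raised risk. The second understates the difference and sets overlapping, correlated estimates against each other.

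**Working it through.** The plan states no figure on this point, so there is none to reproduce.

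**Step 1: coverage of the strata.** The listed strata (0-5, 6-11, 12-17, ≥65) together cover 0-17 and 65 upwards. The uncovered range is 18-64, which is 64 − 18 + 1 = 47 single-year ages. With 18-64 added, the five strata cover every age without gap or overlap.

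**Step 2: which comparators remain.**

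- *Another listed stratum*, for example ≥65 against 12-17. The estimates are disjoint, but the article calls both groups vulnerable.
- *The all-age pooled estimate.* It includes 18-64, but also all the vulnerable strata.

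**Step 3: what the all-age comparator does to the contrast.** Let w be the share of expected visits in the vulnerable age groups, RR_v their relative risk (taken as common to them) and RR_0 the relative risk at 18-64. Approximately,

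RR_all = w·RR_v + (1 − w)·RR_0,

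and so

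RR_v − RR_all = (1 − w)·(RR_v − RR_0).

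The contrast is reduced for any w above zero whenever the two effects differ. The documents give neither w nor the relative risks. The values below are assumptions, with RR_v = 1.10 and RR_0 = 1.02, so that the true difference is 0.08:

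| w (assumed) | Share of contrast kept, 1 − w | Difference seen |
|---|---|---|
| 0.30 | 0.70 | 0.70 × 0.08 = 0.056 |
| 0.45 | 0.55 | 0.55 × 0.08 = 0.044 |
| 0.60 | 0.40 | 0.40 × 0.08 = 0.032 |

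**Step 4: the same on the ratio scale, with other assumed values.** Take RR_v = 1.08 and RR_0 = 1.02. The true ratio is 1.08/1.02 = 1.059.

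- Share aged 18-64 of 0.45: RR_all = 0.45 × 1.02 + 0.55 × 1.08 = 1.053; ratio 1.08/1.053 = 1.026.
- Share of 0.50: RR_all = 1.050; ratio 1.029.
- Share of 0.58: RR_all = 0.58 × 1.02 + 0.42 × 1.08 = 1.045; ratio 1.033.

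On the log scale, 44% to 57% of the contrast is kept (ln 1.026/ln 1.059 to ln 1.033/ln 1.059, from unrounded values).

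The direction follows from the algebra. The size depends entirely on the assumed share and, on the ratio scale, slightly on the assumed relative risks.

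**The case against.** The strongest reply has four parts.

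1. *The objective can be read as a comparison among vulnerable groups.* The wording "assess whether these associations differ across vulnerable patient groups" allows this, and four disjoint strata support it. This stands as far as it goes: some age comparison remains possible. It does not serve the expectation in Anticipated Findings, which sets vulnerable patients against everyone else.

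2. *The plan is not closed.* The strata are introduced as planned, alternative stratifications are foreseen, and analytical decisions are referred to a statistical analysis plan that is not shown. That plan may well include 18-64. But the article does not merely leave the strata open; it lists them, and the list has a gap. A sensitivity analysis with no stated content cannot supply the reference for part of the primary objective.

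3. *The missing counts can be recovered.* The 18-64 count is the all-cause count minus the four listed strata. This is true and shows that the fix is cheap. The article does not say it will be done. Nor does it plan a comparison of strata with the all-age estimate, so Steps 3 and 4 describe a fallback that readers may use, not a stated analysis.

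4. *No formal test is announced.* Anticipated Findings states an expectation and the objective speaks of assessing. This is correct, and the point is worded accordingly.

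A reader might also infer that the ≥65 stratum must be split at 85, because O6 concerns patients aged 85 or older. The documents do not support that. O6 is a separately registered substudy with its own analysis, and the Background itself treats older adults as 65 and over. Counts could also be sparse: 6.35 million/(56 sites × 2,192 days) is about 52 visits per site-day if all sites report throughout. If 6-10% of visits were at age 85 or over (assumption), that would be about 3 to 5 per site-day.

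**Conclusion.** The gap is real. With the strata as listed, the expectation of stronger relative effects in children, adolescents and older patients cannot be checked against a disjoint group that is non-vulnerable by age. The alternatives are other vulnerable strata, or an all-age estimate that shrinks the contrast to 1 − w of its true size. For assumed w of 0.30 to 0.60, that is 70% to 40%. The approximation takes one common relative risk for the vulnerable groups, and no figure in the documents fixes w.

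Two stronger readings are tempting and should be resisted. One is that the effect-modification part of the primary objective cannot be answered at all. The documents do not support this: sex, multimorbidity proxies, deprivation and urban-rural context do not depend on the age list, and contrasts among the listed strata remain. The other is that visits by patients aged 18-64 are lost. They are not: they stay in the all-cause hospital-day counts, and the primary heat-volume estimate is unaffected.

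This should be put right before age-specific findings are reported. It is no reason to doubt the main estimate.

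**What to change.** - Add 18-64 years as a stratum in the same two-stage model and name it as the reference.
- Report each vulnerable stratum as a ratio of pooled cumulative relative risks against 18-64, with a 95% CI that allows for both strata coming from the same sites and days.
- Base any statement of a stronger effect on that ratio, not on whether each stratum is significant by itself.
- If the statistical analysis plan already has this stratum, correct the list in the article to match.
- Date and label the change. The Results section says the retrospective analysis of the overall population is already complete, so readers need to see whether the stratum was added before or after results were known.

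The cost is one more stratum to fit and report, on data already held. A further split of ≥65 at 85 years is optional and not part of the required change.
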